**Effects of brown rice or white rice on glycemic and lipid metabolism, and vascular function**

**1 Background**

We have been reported that high-fiber diet intervention with combination of brown rice and fiber-rich dishes improve endothelial function in patients with type 2 diabetes mellitus (T2DM)1,2. However, it remains unknown whether brown rice is an essential factor to improve endothelial function in these patients. In this study we hypothesized that a simple dietary intervention with brown rice will be acceptable dietary intervention in out-patients and improve vascular function through change in glycemic and lipid metabolism.

**2 Study objectives**

To evaluate the effect of brown rice or white rice-based diet intervention on glycemic　and lipid metabolism, and vascular function.

**3 Study design and schedule**

**3.1 Patients**

Patients with T2DM will be invited to participate at the Shiga University of Medical Science Hospital. Shiga, Japan.

**Inclusion criteria:**

1) T2DM aged between 40 and 80 years

2) HbA1c < 8.0% (JDS)

3) Patients who don't use insulin therapy

4) Patients who don't take alpha-glycosidase inhibitor (alpha-GI)

5) no smoking

**Exclusion criteria**

1) Patients with severe vascular, hepatic, renal, cancer, and/or infectious disease

2) Patients who changes drug treatment within 2 months

3) Patients with rapid weight loss

4) Patients who enrolled in another study within 1 month

5) Patients who have eaten brown rice

6) Patients who have taken fiber supplement

7) Pregnancy and breast-feeding patient

8) Patients who have taken warfarin and NSAIDS

**3.2 Number of patients**

30 patients (15 patients per group, 2 groups) Brown rice group, White rice group

**3.2.1 Rationale for setting the number of patients**

We calculated our sample size using results from a preliminary study, in which an intervention of a brown rice diet increased FDR* by 83.1 ± 60.2% and a white rice diet increased FDR by 19.5 ± 40.9% (unpublished data). We estimated that with a sample size of 30, the study would have 80% power to detect differences in the outcome between randomized groups, assuming an overall lost-to-follow-up rate of 14% with a type 1 error of 5% (two-sided).

* flow debt repayment: one of the endothelial function

**3.3 Intervention**

Intervention: Brown rice

Control: White rice

**3.4 Intervention procedure**

A feasible intervention protocol for a clinical setting has been chosen for both groups. Both brown rice (for the fiber-rich diet) and white rice will be provided in small single-serve pouches and shipped to subjects for the 8 weeks to limit energy intake (provided by Sunstar Inc., Osaka, Japan). Barley and amaranth are blended with brown rice by the company to adjust the viscosity and flavor. In the brown rice diet group, participants will be instructed to consume brown rice as a staple food for 10 out of 21 meals per week and to maintain energy intake at 28–30 kcal/kg for 8 weeks. Similarly, in the white rice diet group, participants will be instructed to consume white rice as a staple food for 10 out of 21 meals per week and to maintain energy intake at 28–30 kcal/kg for 8 weeks.

**3.5 Study design and schedule**

**3.5.1 Study design and schedule**

a randomized, open-labeled, parallel-controlled trial

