**3.11 Randomization**

Randomization will be stratified by minimization method with age (66 years old), sex, and body mass index (24). After the run-in period, participants will be randomly assigned to a brown rice or white rice diet. Investigators will be provided with a random allocation sequence that will be made by a research assistant, who is independent of the investigators, using computer-generated random digits.

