**4.1 Primary outcomes**

The primary outcome of the present study is change in endothelial function both in fasting and in postprandial state.

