**6 Statistical analysis**

The peak forearm blood flow (FBF) response, duration of reactive hyperemia (RH), and total reactive hyperemic flow (flow debt repayment (FDR)) will be used to assess the resistance of vessel endothelial function. Changes in endothelial function will be analyzed by paired t-test. Differences in change of endothelial function will be analyzed by unpaired t-test.

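### Nothing in the open-label protocol keeps whoever derives the primary blood-flow measures unaware of arm or visit; coded derivation would reduce any bias at that step at small cost

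*Protocol*

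**What the plan says.** Section 3.5.1 of the protocol gives the design as "a randomized, open-labeled, parallel-controlled trial" and makes no exception for outcome assessment.

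Section 3.11 states: "Investigators will be provided with a random allocation sequence that will be made by a research assistant, who is independent of the investigators".

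Section 4.1 states: "The primary outcome of the present study is change in endothelial function both in fasting and in postprandial state". Section 6 says how it is measured: "The peak forearm blood flow (FBF) response, duration of reactive hyperemia (RH), and total reactive hyperemic flow (flow debt repayment (FDR)) will be used". For the comparison of the arms it adds: "Differences in change of endothelial function will be analyzed by unpaired t-test".

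Section 11.3 sends blood, urine, bacterial flora and lipid metabolites to outside laboratories. The endothelial measurement is not on that list. The protocol does not say who acquires or derives the blood-flow values, on what device, whether traces are stored, or whether the person deriving them knows the arm or the visit.

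**The concern.** Brown and white rice cannot be hidden from the people who eat them, so an open label for participants is unavoidable. Deriving a number from a blood-flow measurement is a separate step and can often be masked even when the intervention cannot. The protocol declares the whole trial open, gives the allocation sequence to the investigators, and puts nothing between arm identity and the derivation of the three primary measures.

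Duration of RH and total hyperemic flow both depend on where the response is taken to start and end. If that point is a matter of judgement, a person who knows the arm could lean, without intent, towards the result that section 1 hypothesises. Such a lean would enter the unpaired comparison of changes directly and look like a diet effect. Many secondary outcomes have some separation from the study team because an outside laboratory produces them. The protocol names no such separation for the primary outcome.

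This is not a detail to leave to a later analysis plan. Who is masked is a matter of conduct and is best settled before values are derived.

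**Working it through.** **1. Text check.** Taken side by side:

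| Question | Protocol | Answer |
|---|---|---|
| Is the trial masked at any level? | 3.5.1 | No; open-label without exception |
| Who receives the allocation sequence? | 3.11 | The investigators |
| What is the primary outcome derived from? | 4.1, 6 | Peak FBF, RH duration, FDR |
| Does an outside laboratory derive it? | 11.3 | None is listed for it |
| Is the person deriving it kept unaware of arm or visit? | Nowhere | Not stated |

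**2. Inputs for an illustration.** Section 3.2.1 reports that "an intervention of a brown rice diet increased FDR* by 83.1 ± 60.2"%, against 19.5 ± 40.9% for white rice. It plans 30 patients (15 per group, section 3.2), 80% power, two-sided 5% and 14% loss to follow-up.

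- Planned contrast: 83.1 − 19.5 = 63.6 points of FDR change.
- Pooled SD: √[(60.2² + 40.9²)/2] = √[(3624.04 + 1672.81)/2] = 51.46.
- Standardised difference: 63.6/51.46 = 1.24.

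**3. The plan's own figure first.** With the exact (noncentral t) calculation, 11 per arm gives 78.7% power and 12 per arm gives 82.5%. So 24 evaluable patients are needed, and 24/0.86 = 27.9, that is 28 enrolled. The planned 30 covers this. In the other direction, 30 × 0.86 = 25.8, about 13 evaluable per arm, with power 85.6%. The sample size is sound, and masking would change neither it nor alpha.

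**4. Effect of an assumed differential error.** Suppose there is no true effect, but the derivation shifts the contrast between arms by *b* points. The standard error of the contrast is 51.46 × √(2/13) = 20.19. The noncentrality is *b*/20.19 on 24 degrees of freedom, and the two-sided 5% critical value is 2.064.

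| *b* (FDR points) | Share of 63.6 | Noncentrality | Two-sided rejection | Of which favouring brown rice |
|---|---|---|---|---|
| 0 | 0% | 0 | 5.0% | 2.5% |
| 5 | 8% | 0.248 | 5.7% | 4.3% |
| 10 | 16% | 0.495 | 7.6% | 6.9% |
| 15 | 24% | 0.743 | 11.0% | 10.6% |
| 20 | 31% | 0.991 | 15.8% | 15.7% |

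The last column takes the shift to favour brown rice. The values of *b* are assumptions; the protocol gives no basis for choosing among them. At 5 points the two-sided effect is slight, and at 15 to 20 points it is not.

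**5. What coding can and cannot reach.** Coded data remove arm and visit from the derivation step. They do nothing at acquisition. Under section 3.8 each group eats its own rice in the tolerance test, so an operator present at a postprandial measurement may see which rice was eaten. They do not affect participants' behaviour either. Giving the allocation sequence to the investigators is a matter of allocation concealment, and coding does not change that.

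**The case against.** The strongest reply is that the point rests on silence. Open-label is a correct description of a diet trial, and no section says that the person deriving the values knows the arm. Masked handling could sit in a measurement procedure that is not shown. The mechanism is also inferred: section 6 names three quantities but no device, stored trace, manual reading or software. If the values come out automatically, there is little room for bias. And section 3.11 gives the independent research assistant only one task, making the sequence, so that person's availability for coding is not established.

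Much of this stands. Operator judgement has to be a condition of the point, not a fact, and the size of any error is unknown. What does not stand is that silence settles it. Masking of outcome assessment is ordinarily a protocol matter, and the only statement on masking here is open-label. If derivation is automated, one sentence saying so would close the point.

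A reader might infer more than the text supports, in four ways:

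- *That the primary outcome is read unmasked by judgement.* The protocol does not say who reads it or how. Receiving the allocation sequence does not show that an investigator also derives the values.
- *That the bias could never be undone.* If data are stored, they can be coded and read again masked. If they are not stored, file coding cannot be applied at all. Irremovable bias and a simple coding remedy cannot both be claimed without qualification.
- *That coding would prevent bias.* It acts on derivation only.
- *That the remedy adds no procedure.* It needs no new reader, patient or patient procedure, but coding, custody of the code and a lock on the values are new steps.

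**Conclusion.** The point holds in a limited form. The protocol leaves open an avoidable route by which knowledge of the arm could reach the derivation of the primary outcome. This is a weakness in a design choice; it is not evidence that bias occurred or would occur. It is worth correcting because the change is small and protects the primary contrast, but it does not undermine the sample size or the planned test.

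Any effect depends on how far the derivation relies on judgement. Under assumed differential errors of 5 to 20 FDR points, with SD 51.5, 13 evaluable per arm and no true effect, the two-sided false-positive rate runs from 5.7% to 15.8% against a nominal 5%. With automated derivation the effect could be negligible. Confidence is medium, because stored data and operator judgement are both inferred from the quantities named in section 6.

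**What to change.** Add to sections 3.11 and 6 wording to this effect:

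*Where forearm blood-flow data are stored, a person not involved in reading them (for example the independent research assistant who makes the allocation sequence) replaces participant, arm and visit labels by a code. The existing reader derives peak FBF, RH duration and FDR from the coded data. The code is broken only after all values are locked.*

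If the values are produced automatically, or are read live with nothing stored, the protocol should say so, since the first makes coding close to a formality and the second makes it impossible as written.

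The cost is modest file handling, custody of the code and a short delay before results can be seen by arm. It needs no additional reader, patient or patient procedure, and leaves the sample size, alpha and analysis unchanged. The text should claim only reduced bias at derivation. Acquisition, participant behaviour and allocation concealment remain outside its reach.

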**3.5.2 Study period**

Study period: from ethical review committee approval to March 31, 2014

(IRB approval date for original protocol: September 20, 2011)

**3.6 Study schedule (Figure 1)**

**3.6.1 Run-in period**

Eligible patients undergo a 4- to 8-week run-in period to maintain a stable diet and assess tolerability. Participants will be advised by a dietician to have a standard diet for diabetes, consisting of 28–30 kcal/kg of ideal bodyweight (protein 15%, fat 25%, carbohydrate 60%) at the beginning of the run-in period.

**3.6.2 Intervention period (2 months)**

After the run-in period, participants will be randomly assigned to a brown rice or white rice diet. Both brown rice and white rice will be provided in small single-serve pouches for the 8-week study to limit energy intake. Participants will be instructed to consume provided pouches as a staple food for 10 out of 21 meals per week and to maintain energy intake at 28–30 kcal/kg for 8 weeks.

**3.6.3 Energy control period (2 months)**

After the intervention period, participants will be instructed to maintain energy intake at 28–30 kcal/kg for 8 weeks. During this period, participants will not be allowed to consume brown rice.

**3.6.4 Follow up period (2 months)**

After the energy control period, all participants can have un-restricted diet without dietitian’s advice.

[figure not shown]
Figure 1 Study schedule

**3.7 Dietary assessment**

During the run-in, intervention, and energy control periods, a dietician will provide participants with written and verbal instructions regarding the completion of a 3-day dietary record with a digital photograph of each meal. A camera will be provided to participants right before dietary assessment.

**3.8 Meal tolerance test**

A rice tolerance test will be performed before and after the intervention. The participants in each group ingests an isocaloric (250 kcal) amount of brown or white rice. The nutritional composition of both brown rice and white rice is shown in Table 1.

Table 1. Nutritional composition of both brown rice and white rice

(100g)

|  | Brown rice | White rice |
| --- | --- | --- |
| Energy (kcal) | 115 | 155 |
| Protein (g) | 2.5 | 2.6 |
| Fat (g) | 1.0 | 0.4 |
| Carbohydrate (g) | 23.2 | 35.2 |
| Fiber (g) | 1.8 | <0.5 |

(Japan Food Analysis Center)

**3.9 Medications (Include supplements)**

During run-in and intervention period (4 months), addition, dosage changes, or discontinuation of any medications should not be performed as a rule. In case of hypoglycemia, dosage changes or withdrawal is permitted. However, a description of the procedure needs to be recorded on the case report form. In addition, any supplements should not be permitted.

**3.10 Honorarium**

　 After the follow up period, all participants will receive single-serve pouches with brown rice provided by Sunstar Inc.

**3.11 Randomization**

Randomization will be stratified by minimization method with age (66 years old), sex, and body mass index (24). After the run-in period, participants will be randomly assigned to a brown rice or white rice diet. Investigators will be provided with a random allocation sequence that will be made by a research assistant, who is independent of the investigators, using computer-generated random digits.

**4 Outcomes**

Change in outcomes between 2 month and 0 month. In addition carryover effect will be analyzed at 4 month.

**4.1 Primary outcomes**

The primary outcome of the present study is change in endothelial function both in fasting and in postprandial state.

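### The primary outcome covers up to six between-arm comparisons with no success rule, while the stated 80% power and 5% error belong to a single FDR comparison in an unnamed state

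*Protocol*

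**What the plan says.** Four places in the protocol bear on this point.

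- **Section 4.1** defines the primary outcome: "The primary outcome of the present study is change in endothelial function both in fasting and in postprandial state". It gives two states and names no index.
- **Section 4** fixes the time frame: "Change in outcomes between 2 month and 0 month". Month 4 is kept for carryover.
- **Section 6** lists the measures: "The peak forearm blood flow (FBF) response, duration of reactive hyperemia (RH), and total reactive hyperemic flow (flow debt repayment (FDR)) will be used". None is ranked above the others. On the comparison between arms it says: "Differences in change of endothelial function will be analyzed by unpaired t-test".
- **Section 3.2.1** sets the sample size from preliminary results in which "an intervention of a brown rice diet increased FDR* by 83.1 ± 60.2"% and "a white rice diet increased FDR by 19.5 ± 40.9"%. The conclusion is: "We estimated that with a sample size of 30, the study would have 80% power to detect differences in the outcome between randomized groups", with 14% loss to follow-up and a two-sided type 1 error of 5%. The footnote describes FDR as "flow debt repayment: one of the endothelial function", so it does not single FDR out as the primary. The section does not say whether the preliminary FDR was fasting or postprandial.

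**The concern.** Three indices in two states make up to six between-arm comparisons under one primary outcome. The protocol does not say whether one positive result is enough, whether both states must be positive, or whether one index leads. The sample-size section nevertheless speaks of one outcome, with one effect, one power and one error rate.

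The interpretation of the main result is at stake. The trial is small and open-label. Without a named primary comparison, a positive claim could rest on whichever index and state falls below 0.05, and a reader could not tell whether that was the comparison the trial was sized for. Under a stricter rule, the trial may have less power than it states.

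**Working it through.** **Inputs.** From section 3.2.1: FDR change 83.1 (SD 60.2) on brown rice and 19.5 (SD 40.9) on white rice, two-sided 5%, 14% loss. From section 3.2: 15 per arm. From sections 4.1 and 6: 2 states × 3 indices = 6 comparisons, each by unpaired t-test. Assumed, because the protocol gives no values: the correlation between comparisons (equal for all pairs, 0 to 0.9), and the preliminary FDR effect for every index and state wherever power is computed.

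**Step 1: reproduce the plan's figure.**
- Difference = 83.1 − 19.5 = 63.6.
- Pooled SD = √((60.2² + 40.9²)/2) = 51.46.
- Standardised effect = 63.6/51.46 = 1.236.
- Noncentral t power at two-sided 5%: 78.7% at 11 per arm, 82.5% at 12, 85.6% at 13.
- So 12 per arm are needed, 24 in total, and 24/0.86 = 27.9, or 28 patients.

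The stated 30 is within two patients of this. With 14% loss, 15 × 0.86 = 12.9, so about 13 per arm are evaluable. The calculation is sound for one FDR test.

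**Step 2: error if any comparison counts.** Under independence the false positive rate is 1 − 0.95^k: 9.75% for k = 2 (FDR in either state) and 26.5% for k = 6. With correlation, simulation at 13 per arm with each test at 5% gives:

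| Assumed correlation | FDR in either state (k = 2) | Any of six (k = 6) |
|---|---|---|
| 0 | 10% | 26% |
| 0.5 | 9% | 21% |
| 0.7 | 8–9% | 17% |
| 0.8 | 8% | 14% |
| 0.9 | 7% | 11% |

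**Step 3: power if all must succeed.** Error now stays at or below 5%. Under independence, joint power at 13 per arm is 0.856² = 73% for FDR in both states and 0.856⁶ = 39% for all six. Simulation with correlation gives:

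| Assumed correlation | FDR in both states | All six |
|---|---|---|
| 0 | 73% | 39% |
| 0.5 | 77% | 58% |
| 0.7 | 78% | 65% |
| 0.8 | 80% | 69% |
| 0.9 | 81–82% | 75% |

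**Step 4: price of an adjustment.** With Bonferroni at 13 per arm, power per test is 77.1% for k = 2 (α = 0.025) and 61.2% for k = 6 (α = 0.05/6). Keeping 80% per test needs 14 per arm, 28/0.86 → 33 patients, for k = 2, and 18 per arm, 36/0.86 → 42 patients, for k = 6. One named primary comparison needs no increase.

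**The case against.** Several points can fairly be made for the protocol.

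- **Six tests at 5% each is an inference.** Section 6 states no per-test level and no success rule. It says three measures describe one construct, and section 4.1 may mean only that function is measured in two states. This stands: the documents do not say that any one of six results would count as success. They do not exclude it either, and that gap is the defect.
- **Independence is implausible.** FDR is the total hyperemic flow, so it comes from the same response as peak flow and duration. This stands, and 26% is a ceiling. If FDR is taken as the index, as section 3.2.1 suggests, the rate is only 7% to 10%, still above the stated 5%.
- **Power need not fall below 80%.** A reader might infer that requiring both states always misses the stated power. The documents do not support that. Thirteen per arm gives 85.6% per test, not 80%, and joint power reaches about 80% at a correlation of about 0.8 or more if the effect is the same in both states.
- **Testing order and alpha handling often sit in the SAP, which is not shown.** This stands for the procedure. It does not cover naming the primary variable and matching the sample size to it. Those belong in the protocol, and here the two sections do not agree.

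**Conclusion.** The concern holds in this form: the power and error in section 3.2.1 are right for one FDR comparison and do not describe the primary outcome of sections 4.1 and 6.

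The consequence depends on the unstated success rule. If any comparison counts, the false positive rate is about 11% to 21% at correlations of 0.9 to 0.5, or 7% to 10% if only FDR in either state counts. If FDR must succeed in both states, power is about 73% to 80% at correlations of 0 to 0.8; if all six must succeed, it is about 39% to 75% at correlations of 0 to 0.9.

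A reader might infer that error and power fail together. They do not: inflated error belongs to the any-success rule and lost power to the all-must-succeed rule. Nor is the sample-size arithmetic wrong.

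The mismatch itself rests on the text alone. The sizes rest on assumed correlations, and the power figures also on the preliminary FDR effect applying to every index and state. The protocol gives no effect or SD for peak FBF, RH duration or a second state.

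**What to change.** 1. In section 4.1, name one primary outcome: the between-arm difference in change in FDR from 0 to 2 months, in the state in which the preliminary data of section 3.2.1 were measured. The sponsor must confirm that state and write it into section 3.2.1. Choosing fasting or postprandial before this is confirmed could attach the 80% power to a comparison it was not computed for.
2. Test FDR in the other state next, at two-sided 5%, only if the first comparison is significant.
3. Move peak FBF and duration of RH to the secondary outcomes in section 4.2, and align section 6.
4. State in section 3.2.1 that the 80% power and 5% error apply to that one FDR comparison.

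The cost is a short amendment to sections 3.2.1, 4.1, 4.2 and 6. The sample size of 30 stands, and no patients, visits or measurements are added. The small downside is that peak FBF and RH duration can no longer carry a primary claim.
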